### Composite primary objective

A primary objective is to determine if surgical excision and sub-dermal injection of triamcinolone acetonide at the time of subsequent caesarean section is effective in preventing or reducing the amount of keloid formation in patients with a previous history of keloid scar after caesarean section. We also aim to investigate whether the appearance and specification of the keloid scar changes after the intervention (type of response).

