### Composite primary outcome

The primary outcomes are:Reduction in the amount of keloid formation after the intervention in patients with a previous history of keloid caesarean scarChanges in the appearance and specification of the keloid scar after the intervention.

The baseline information including measurement of the scar will be collected at the time of consent and/or around 36 weeks when the patient is consented for the surgery. The scar will be photographed and measured for length and width in millimetres; elevation, hardness and erythema will be graded by the assessor on a 3-point scale (0 = none, 1 = partial, 2 = along entire scar). A subjective symptom score will be graded by the patient for pruritus, pain and swelling on a 3-point scale (0 = none, 1 = occasionally, 2 = all the time).

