### Outcome measures

#### Data collection sheet

A purposefully designed questionnaire consisting of two sections will be used to collect demographics (including age, country of birth, ethnic background, weight, height, BMI, number of previous vaginal births and/or caesarean sections, number of previous miscarriages, abortion and stillbirth, family history of keloid scars, history of any previous surgery and keloid scar on another site of body, gestational age at the time of baseline assessment) and any prior treatment of the keloid scar (section 1) and data on the keloid scar (section 2) including redness, hardness and elevation of the scar compared to the surrounding skin (0 = none, 1 = partially, 2 = entire scar). This section of the questionnaire also enquires about subjective symptoms of the scar including, but not limited to, itching, pain and swelling (0 = none, 1 = occasionally, 2 = all the time). The scar will be measured in millimetres using a hardened stainless steel 150mm Digital Vernier Caliper (Kincrome Pty Ltd, Scoresby, Australia) with a liquid-crystal display (LCD) screen to read an accurate measure to the nearest 0.02 mm. We will also take photographs of the scar to compare the visual changes. Section 2 of the questionnaire will be used at follow-up visits to collect data on the changes in the keloid scar. The same 150mm Digital Vernier Caliper will be used at follow-up visits, and the scars will be photographed again. To improve the objective validity of the trial and minimise recall bias of patients in the symptom scores, the participants will be shown photographs of the scar both before and one year after the intervention. They will be asked if they see any improvement before and after participating in the trial, both before and after seeing their scar photographs. In addition, the participants will assess and grade their satisfaction with the treatment on a 4-point scale (0 = no improvement/poor, 1 = fair, 2 = good, 3 = excellent). The participants will be queried on their overall satisfaction with the treatment (5 = very satisfied, 4 = slightly satisfied, 3 = neutral satisfaction, 2 = slightly unsatisfied, 1 = very unsatisfied). They will also be asked if they think they were in the intervention arm or the control arm of the trial before revealing this information to them at the final visit.

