#### Depression, Anxiety and Stress Scale-21 (DASS-21)

The DASS-21 is the short version of the DASS-42 questionnaire. It contains a set of three self-report scales and will be used to measure anxiety, depression and stress during pregnancy and after childbirth. The DASS-21 has been shown to have high internal consistency and to yield meaningful discriminations in a variety of settings. It should meet the needs of both researchers and clinicians who wish to measure current state or change in state over time on the three dimensions of depression, anxiety and stress. The tool has been used in previous studies on perinatal women in Australia, Canada, Chile, England, Germany, Iceland, New Zealand and the USA with reasonable response rates [14, 15]. Each of the three DASS-21 scales contains 7 items. The Depression scale assesses dysphoria, hopelessness, devaluation of life, self-deprecation, lack of interest/involvement, anhedonia and inertia. The Anxiety scale assesses autonomic arousal, skeletal muscle effects, situational anxiety and subjective experience of anxious affect. The Stress scale is sensitive to levels of chronic non-specific arousal. It assesses difficulty relaxing, nervous arousal and being easily upset/agitated, irritable/over-reactive and impatient. Respondents are asked to use 4-point severity/frequency scales to rate the extent to which they have experienced each state over the past week. Scores for Depression, Anxiety and Stress are calculated by summing the scores for the relevant items and then multiplying each scale score by 2. Then, each score can be transferred to the DASS profile sheet, enabling comparisons to be made between the three scales and also giving percentile rankings and severity labels as shown in the following table.

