### Procedures

All eligible women will be approached at the time of booking into the clinic for caesarean section at around 36 weeks and will be given information about the study. Those women who meet the inclusion criteria and sign the informed consent form will be randomised to either the intervention or the control group by the independent researcher as explained previously (Fig. 1). On the day of the caesarean section, the sealed envelope containing instructions for the type of treatment will be picked up by the surgeon. The surgeon opens the envelope when the woman is ready for the caesarean section.

The control group will receive surgical excision of the keloid scar at the beginning of the procedure during skin incision. The baby will be delivered as normal, and routine wound closure will be performed in accordance with National Institute for Health and Care Excellence (NICE) guidelines as follows: The uterus is closed in two layers followed by closure of the rectus sheath, all using continuous sutures with 1-Vicryl (Johnson & Johnson). The fat layer is closed with interrupted plain gut sutures 2 cm apart. The skin layer is then closed with 3-0 Monocryl (Ethicon) in a sub-cuticular fashion.

The intervention group will receive surgical excision of the keloid scar after the delivery of the baby. Closure of the uterus layers, rectus sheath and the fat layer are completed as explained above. Then, triamcinolone acetone will be injected sub-dermally at the time of wound closure. Two ampules of triamcinolone acetonide (Kenacort®-A 10 suspension, Aspen Pharma Pty Ltd) will be administered at a single dose; each ampule contains 10 mg/1 ml active medication. The surgeon will inject one ampule along the entire length of the upper edge of the skin incision and one ampule along the entire length of the lower edge of the skin incision, using a 25 G needle.

After the procedure is completed, the surgeon will fill in the post-operation survey. The excision of the scar and administration of the injection will be performed by the surgeon who is scheduled to perform the surgery on that day. All the surgeons in the Department of Women’s and Newborn Health will be trained on how to perform the excision and injection of the triamcinolone. The Principal Investigator of the study will assess the fidelity to the intervention by supervising procedures.

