### Data analysis

Intention-to-treat analysis will be performed using SPSS Advanced Statistics version 24.0 (SPSS, Chicago, IL, USA). Descriptive statistics will be used to summarise the demographic data; binary outcomes will be summarised with a relative risk (RR) and 95% confidence intervals (CIs) and compared between the two groups using a χ^2^ test (or Fisher’s exact test where applicable). Comparison of the number of patients with keloid formations within groups and between the two groups will be done using a χ^2^ test. A *t* test will be used to assess continuous non-skewed variables; these will be presented as means with standard deviations. For skewed ordinal data, the Mann–Whitney *U* test will be used; these data will be presented as medians with interquartile ranges. Difference in the effect over the sub-groups will be assessed using logistic regression. Outcomes of interest will be number of patients with keloid formation, changes in the appearance and specification of the keloid scar, depression, anxiety, stress and patient’s satisfaction. Changes in the appearance and specification of the keloid scar after the intervention will be summarised into two groups (binary outcome: 0 = changed, 1 = not changed) and will be analysed using logistic regression adjusting for the number of keloids formed and demographic variables. A *p* < 0.05 will be considered statistically significant.

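### The second primary outcome, scar appearance and specification, is coded changed or not changed with no direction, so a worse scar scores the same as a better one

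*Protocol article*

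**What the plan says.** The Composite primary outcome section of the protocol article lists two primary outcomes. The first is directional: a reduction in the amount of keloid formation. The second is change in the appearance and specification of the scar. The Composite primary objective section words its aim equally neutrally, as to "investigate whether the appearance and specification of the keloid scar changes after the intervention (type of response".

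The Data analysis section fixes how the second outcome is handled. "Changes in the appearance and specification of the keloid scar after the intervention" are variables that "will be summarised into two groups (binary outcome: 0 = changed, 1 = not changed", and the binary variable goes into a logistic regression adjusted for the number of keloids formed and demographic variables. No other analysis is assigned to this outcome by name.

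The underlying data are richer. "The scar will be photographed and measured for length and width in millimetres", the assessor grades elevation, hardness and erythema from 0 to 2, and the patient grades itching, pain and swelling from 0 to 2. The caliper is said "to read an accurate measure to the nearest 0.02 mm". The Follow-up section applies the same scales at 6 weeks, 6 months and 12 months.

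Both arms lose the old scar. Under Procedures, "The control group will receive surgical excision of the keloid scar", and the intervention group has excision plus the injection.

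**The concern.** The trial is a superiority trial whose hypothesis is that the injection reduces recurrence. An outcome that serves that hypothesis must separate women who get better from women who get worse. The stated code does not.

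Worsening is also foreseeable. The Background says that surgical removal alone is followed, in 50–100% of cases, by regrowth worse than the original. Excision alone is the control arm. A control patient whose keloid returns larger and a treated patient whose scar resolves would both be coded 0.

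Two things are at stake. A real benefit may be hidden, because improvement on the injection is offset by worsening on control within the same category. And a difference, if found, has no clear meaning: more 'changed' women in one arm could reflect benefit, harm or a mixture.

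**Working it through.** **Inputs from the protocol (Sample size section).** Efficacy 45% v 70%, two-sided 5%, 80% power, 75 per group, 10% allowance for non-compliance. These are directional rates.

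**Step 1: reproduce the stated size.** The pooled two-proportion formula gives 61 per arm without continuity correction and 68 with it. Adding 10%: 68 × 1.1 = 74.8, so 75 per arm and 150 in total, as stated. (68 / 0.9 = 75.6, so 76 per arm, is the near alternative.) The stated number is therefore consistent with a directional efficacy rate.

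**Step 2: power with a directional code.** With n per arm, d the difference in proportions and p̄ their mean,

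power = Φ{ [d − 1.96 √(2p̄(1−p̄)/n)] / √([p₁(1−p₁) + p₂(1−p₂)]/n) }.

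For 45% v 70% and n = 75: d = 0.25 and p̄ = 0.575. The two standard errors are 0.0807 and 0.0781, so the bracket is (0.25 − 1.96 × 0.0807)/0.0781 = 1.175 and power is 0.88. This omits the continuity correction and the allowance for non-compliance, which is why it exceeds 0.80.

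**Step 3: power with the stated code.** Let w be the share of non-improved women whose scar worsens. The protocol gives no value, so w is an assumption, taken as equal in both arms. Then

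P(changed) = P(improved) + w × P(not improved),

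which gives 0.45 + 0.55w on control and 0.70 + 0.30w on the injection. The difference is 0.25(1 − w).

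| w (assumed) | Control changed | Injection changed | Difference | Power, 75 per arm |
|---|---|---|---|---|
| 0 (same as directional) | 45% | 70% | 25 points | 0.88 |
| 0.25 | 58.75% | 77.5% | 18.75 points | 0.70 |
| 0.50 | 72.5% | 85% | 12.5 points | 0.46 |
| 0.75 | 86.25% | 92.5% | 6.25 points | 0.24 |
| 0.90 | 94.5% | 97% | 2.5 points | 0.11 |

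The true benefit is 25 points in every row; only the coding differs. The figures are for an unadjusted comparison.

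**Step 4: what if worsening is not shared equally?** Suppose 45% improve and 45% worsen on control, and 70% improve and 20% worsen on the injection. Both arms are then 90% changed (45 + 45 and 70 + 20), and the 25-point benefit shows as no difference. This example is constructed. It shows that full cancellation is possible, not that it is expected.

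**The case against.** **The details may sit elsewhere.** An article may leave the threshold, the rule for combining items and the visit to the full protocol or analysis plan, so their absence is not a fault here. That is right, and the point does not rest on them. The two-way code itself is stated, and a threshold added later would not give it a direction; only replacing the code would.

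**'Changed' may be meant as 'improved'.** Possibly, but neither the objective, the outcome nor the analysis says so. If that is the intention, the correction is short.

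**Other analyses are planned.** The Data analysis section says a t "test will be used to assess continuous non-skewed variables", adds a Mann–Whitney test for skewed ordinal data, and lists scar changes among the outcomes of interest. A reader might infer from the binary code that the millimetre measurements and grades are thrown away. The document does not support that: they leave only the one analysis named for this primary outcome. The generic tests still do not repair that analysis.

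**The main question is partly protected.** Keloid formation is directional, has its own χ² comparison and is the outcome for the interim analysis. This stands and limits the damage to one of two primary outcomes.

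**Near-universal change is not established.** Both arms have the scar excised, readings go to 0.02 mm, and no minimum change is stated. A reader might infer that nearly every woman would be 'changed' and that the outcome could show nothing. If any caliper difference counted, the chance of an identical reading on one dimension would be about 1.6%, 0.8% or 0.2% for an assumed SD of change of 0.5, 1 or 5 mm. But 0.02 mm is given only as the instrument's resolution, and nothing says that such a difference is enough. This remains an inference.

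**Baseline adjustment is a separate matter.** Unadjusted tests are valid after randomisation, so leaving baseline values out of the t and Mann–Whitney tests is not an error. For DASS-21, the stated secondary outcome is the percentage of women affected, which adjusting the scores would not address.

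**Conclusion.** The point holds for the missing direction. Followed as written, the rule for the second primary outcome puts regrowth and resolution in one category, and its odds ratio cannot be interpreted as efficacy. This is a flaw in what is stated, not a missing detail, and should be corrected before analysis.

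The size depends on how many non-improved women get worse, which the protocol does not give. Over assumed shares of 25% to 90%, equal in both arms, power falls from about 0.88 to between 0.70 and 0.11. This borrows the plan's 45% v 70% as improvement rates for scar appearance, which is itself an assumption. The direction of the loss is certain whenever some women worsen and the share is equal in both arms; its amount is not.

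It would go too far to say that the outcome cannot show any effect. The contrast vanishes only at the extreme of the equal-share model, or where worsening happens to balance improvement.

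**What to change.** In the Data analysis section, replace the code with a directional one: at 12 months, relative to baseline, improved v same or worse. The minimum change that counts as improvement should be set before unblinding. The new definition should also settle how the items are combined if the full protocol does not already do so. In the Composite primary outcome section, reword the second outcome from change to improvement so that the two sections agree.

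Optionally, report the measured dimensions and grades at 12 months, adjusted for their baseline values, as supporting analyses. They need not become further primary comparisons.

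No new data are needed, since the same scales are used at baseline and at every visit. The change is still more than editorial. The trial is registered and recruitment began in May 2019, so it alters a primary outcome's definition mid-trial and should be documented as an amendment, with its date and reason, while the statistician and outcome assessor remain blinded.

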### Sample size

Using the estimates from the study by Khalid et al. [13], the intervention will increase the incidence of efficacy of treatment for keloid scarring from 45% in the excision followed by radiation group to 70% in the excision followed by intralesional triamcinolone acetonide and 5-fluorouracil group. We calculated that a total of 150 patients (75 in each group) would provide 80% power with a two-sided significance level of 5% to detect this difference between the groups. This allows for 10% non-compliance.

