### Follow-up

The follow-up period consists of 12 months face-to-face visits (Fig. 1). Post-operation, the patients will be visited daily on the ward for any signs of potential infectious local complications of the treatment and immediate side effects of the medication injection until the discharge home. The patients will then be visited in the women’s health clinic at the hospital for their 6th week post-partum check. The next follow-up times will be 6 months and 12 months post caesarean section. At each follow-up visit, the same assessment and scoring scales will be used to evaluate the changes to the keloid scar. Late side effects of the medication injection as well as symptoms of depression, anxiety and stress, and participants’ satisfaction will be assessed during follow-up visits at 6 weeks, 6 months and 12 months post-partum. The participants will also be asked if they would recommend such a procedure to another woman with a caesarean section keloid scar (yes/no) and if they would repeat the experience again in a future pregnancy (yes/no).

All measurements at baseline and follow-up visits will be performed by the same researcher, who will also make all efforts to ensure compliance with follow-up. As part of continuous clinical care, patients with any residue keloid scar with be given information on further treatment including referral to plastic surgeons if they are interested (Fig. 2).

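### Baseline scar severity is recorded on the follow-up scales but is not a covariate in the model for change in scar appearance, so precision is forgone and chance imbalance goes uncorrected

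*Protocol article*

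**What the plan says.** Under Composite primary outcome in the protocol article, the second of two primary outcomes is change in the appearance and specification of the scar. The same section states "The baseline information including measurement of the scar will be collected at the time of consent" or at around 36 weeks. Length and width are taken in millimetres. Elevation, hardness and erythema are graded 0 to 2 by the assessor, and itch, pain and swelling 0 to 2 by the patient.

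Under Follow-up, at each visit "the same assessment and scoring scales will be used to evaluate the changes to the keloid scar", and one researcher makes all the measurements.

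Under Data analysis, change in appearance and specification becomes a binary outcome (0 = changed, 1 = not changed) that "will be analysed using logistic regression adjusting for the number of keloids formed and demographic variables". The same section lists chi-square or Fisher tests for binary outcomes and a Mann-Whitney test for skewed ordinal data. It also says that a t test "will be used to assess continuous non-skewed variables; these will be presented as means with standard deviations". A further logistic regression is named for subgroup differences, with no covariates stated.

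Under Randomisation, allocation is 1:1 in permuted blocks of 10. No stratification factor is stated.

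**The concern.** The pre-treatment value of the same measure is often the most useful covariate a trial has. Here it is collected on every woman, on the outcome's own scales, by the same assessor. The article does not simply leave covariates to a later document. It names a set for a primary outcome, and the baseline scar is not in it.

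Two things are at stake. The first is precision: if the starting scar predicts the outcome, leaving it out lowers power at no saving. The second is chance imbalance: if one arm happens to start with larger or more symptomatic scars, neither the stated allocation scheme nor the stated model corrects for it. A decision to adjust taken after the imbalance is seen would be post hoc.

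**Working it through.** **1. Could baseline severity be covered by the stated covariates?** The Data collection sheet section puts demographics and prior scar treatment in section 1 of the questionnaire and scar data in section 2. Demographic variables therefore do not include scar grades or dimensions. The number of keloids formed is not a measure of pre-operative size, grade or symptoms either. (Whether that count belongs in the model at all is a separate question.)

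**2. The plan's own sample size.** Inputs, all from Sample size: assumed efficacy of 45% v 70%; 75 women per arm, a size that "would provide 80% power with a two-sided significance level of 5% to detect this difference between the groups"; and a 10% margin for non-compliance.

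- Uncorrected: n = [1.960·√(2·0.575·0.425) + 0.842·√(0.45·0.55 + 0.70·0.30)]² / 0.25² gives 61 per arm.
- With continuity correction: 68 per arm.
- 68 × 1.10 = 74.8, so 75 per arm and 150 in total. The stated figure reproduces. (68 / 0.9 gives 76 per arm.)

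The point does not disturb the sample size. The 68 evaluable per arm is used below.

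**3. Chance imbalance.** With n per arm, the standardised baseline difference has standard error √(2/n). For n = 75 this is √(2/75) = 0.163.

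- P(|difference| > 0.2) = 2[1 − Φ(0.2/0.163)] = 22%
- P(|difference| > 0.3) = 2[1 − Φ(0.3/0.163)] = 7%

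**4. Power of the binary model.** Two assumptions are needed. The 45% and 70% are applied to changed, although Sample size ties them to efficacy of treatment. The latent correlation rho between baseline severity and outcome is not in the protocol, so a range is used. Simulation: baseline x is standard normal; latent outcome = rho·x + √(1 − rho²)·e; a woman is changed if the latent value falls below Φ⁻¹(p) for her arm. There were 3,000 runs per setting, with a Wald test at two-sided 5% and 68 per arm.

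| rho | Power without baseline | Power with baseline | Gain (points) | Type I error without / with |
|---|---|---|---|---|
| 0 | 83.8% | 84.1% | about 0 | 4.6% / 4.6% |
| 0.3 | 84.6% | 87.0% | about 2 | 5.1% / 5.6% |
| 0.5 | 84.6% | 89.7% | about 5 | 4.8% / 5.0% |
| 0.7 | 83.8% | 94.3% | about 10 | 4.9% / 4.8% |

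The Monte Carlo error of each power is about √(0.85·0.15/3000) = 0.7 points. A second simulation at 75 per arm, indexed by observed covariate-outcome correlation, starts from about 89% and gains about 0, 4 and 6 points at correlations of 0.22, 0.38 and 0.48. At 68 per arm its gains were about 2, 6 and 9. The gain shrinks as enrolment approaches plan. In the first simulation the model without baseline contains arm only; demographic covariates that track scar severity would take up part of the gain.

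**5. If length or width is analysed as continuous.** Set the effect so that an unadjusted comparison of follow-up values has 80% power (noncentrality 1.960 + 0.842 = 2.802). Relative variance is 2(1 − rho) for change from baseline and 1 − rho² for ANCOVA. Power = Φ(2.802/√factor − 1.960).

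| rho | Follow-up only | Change | ANCOVA |
|---|---|---|---|
| 0.3 | 80% | 65.8% | 83.6% |
| 0.5 | 80% | 80.0% | 89.9% |
| 0.7 | 80% | 95.1% | 97.5% |

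ANCOVA is best in every row. A change score does worse than follow-up alone when rho is below 0.5.

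**The case against.** A reader might infer that the baseline scar is not used in any analysis of appearance. The text does not support that. Whether a scar has changed can only be judged against its starting state, so baseline enters when the outcome is derived. It is absent only as a covariate.

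A reader might also take the t test and Mann-Whitney test as the assigned analyses of the scar measures. Those sentences are generic, and the outcomes listed also include depression, anxiety, stress and satisfaction. The only analysis expressly given to appearance is the binary logistic model. The continuous figures therefore apply only if scar dimensions are in fact analysed that way.

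A third tempting argument is that the 0 to 2 grades bound who can change. The coding states no direction: a 0 can rise and a 2 can fall, so either can count as changed. The bound matters only under a directional definition, which the article does not give.

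The strongest objection concerns size. The old scar is excised in both arms, so baseline may predict the outcome only weakly and the gain may be close to zero. Randomisation also keeps the unadjusted comparison valid, and unstratified blocks are acceptable at a single site. All of this stands, and it limits the claim to efficiency and chance imbalance. It does not remove the case for the covariate, since adjustment costs almost nothing when the correlation is low.

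**Conclusion.** The point holds in a limited form. The article fixes a covariate set for a primary outcome and leaves out the baseline scar measures it collects on the same scales. No other listed test takes them as covariates, and no stratification by severity is stated.

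The consequence is forgone precision and uncorrected chance imbalance, not invalidity: simulated type I error is about 5% either way. An imbalance above 0.2 standard deviations would be expected in roughly one trial in five at 75 per arm. The power gain for the binary outcome runs from about 0 to 10 points across latent correlations of 0 to 0.7 at 68 per arm, and is somewhat smaller at full enrolment. That range rests on an undocumented correlation and on borrowing 45% v 70% for changed. A definite loss of power cannot be read from the protocol. The change is worth making because it is nearly free at any correlation.

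**What to change.** Under Data analysis, add the baseline value of the corresponding scar measure as a pre-specified covariate, alongside trial arm, in the logistic model for change in appearance and specification. Where scar length or width is analysed as a continuous measure, replace the unadjusted t test with ANCOVA of the 12-month value on arm and baseline value. Report the unadjusted result as a sensitivity analysis.

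The article defines no summed scar score, so the sentence should name which baseline measure goes with which outcome.

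The cost is a short change to the text and one degree of freedom per model, with almost no loss if the correlation proves near zero. The data are already collected, so no visits, staff or participants are added, and the sample size is unaffected.

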### Hypothesis

Given that triamcinolone acetonide has been used for treatment of keloid scar in other areas of the body [11, 12], we hypothesise that excision of a previous caesarean section keloid scar in conjunction with sub-dermal injection of triamcinolone acetonide will reduce the recurrence and formation of the keloid scar. We would also expect positive patient satisfaction from the treatment and a decline in symptoms of post-partum depression.

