### Interim analysis

An interim analysis will be performed on the primary outcome of keloid formation in patients when enrolling 20 patients, including both the control and intervention groups, by a single statistician who is blinded to allocation and reports the results to the data and safety monitoring committee.

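### The model for the second primary outcome adjusts for keloids formed after randomisation, so its treatment coefficient is not the total effect of allocation

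*Protocol article*

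**What the plan says.** The Composite primary outcome section of the protocol article lists two primary outcomes. The first is "Reduction in the amount of keloid formation after the intervention"; the second is change in how the scar looks and behaves. The Interim analysis section confirms the status of the first: "An interim analysis will be performed on the primary outcome of keloid formation in patients". The Hypothesis section expects that excision with the injection "will reduce the recurrence and formation of the keloid scar".

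The Data analysis section promises an intention-to-treat analysis and treats both as outcomes: "Outcomes of interest will be number of patients with keloid formation, changes in the appearance and specification of the keloid scar". It compares the number of women with keloids between arms by a χ² test. Scar change is reduced to a binary variable (0 for changed, 1 for not changed) and "will be analysed using logistic regression adjusting for the number of keloids formed and demographic variables". An earlier, general sentence in the same section gives binary outcomes a relative risk and a χ² (or Fisher) test.

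**The concern.** A covariate in the model for a randomised comparison should be something that allocation cannot have altered. Here one covariate is a result of the operation under test. Holding it fixed compares arms among women with the same keloid result, so any benefit on the scar that arises because a keloid did not form is taken out of the treatment coefficient.

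There is a second problem. Suppose an unmeasured predisposition drives both keloid formation and scar change, and the injection works. Women in the injection arm who still form a keloid will then, on average, be more predisposed than control women who form one. Women kept free of keloid by the injection will likewise be more predisposed than controls who stay free without it. Conditioning on the keloid result undoes the balance that randomisation created.

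At stake is the interpretation of one of two primary outcomes in a superiority trial that states an intention-to-treat analysis.

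**Working it through.** **1. Timing and role of the covariate.** The Hypothesis section makes keloid formation the target of treatment. The Composite primary outcome and Interim analysis sections make it a primary outcome after the intervention. The Data analysis section then uses keloids formed as a covariate. Baseline history is described in other terms in the Data collection sheet section: keloid at another body site, family history and prior treatment of the scar. Nothing identifies the covariate as a baseline count.

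**2. The plan's own figure.** The Sample size section gives 150 women (75 per arm) for 45% v 70%, 80% power, two-sided 5%, with 10% non-compliance.
- n = [1.960·√(2·0.575·0.425) + 0.842·√(0.45·0.55 + 0.70·0.30)]² / 0.25² = 60.2, so 61 per arm.
- With continuity correction: (60.2/4)·[1 + √(1 + 4/(60.2·0.25))]² ≈ 68 per arm.
- Allowing 10%: 68·1.1 = 74.8, so 75 per arm (150 in all); or 68/0.9 = 75.6, so 76 per arm (152).

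The stated size reproduces. It is not at issue and does not change with the fix.

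**3. What the covariate does to the odds ratio.** Assumptions not in the documents:
- Keloid in 55% of controls and 30% of the injection arm. These are the complements of 45% and 70%, which the Sample size section gives as efficacy in another study's arms, not as keloid rates.
- Keloid treated as yes/no, although the plan says a number.
- The outcome is favourable change, although the plan's coding has no direction. Under the plan's coding the odds ratios would be reciprocals (2.28 becomes 1/2.28 = 0.44).
- The links between keloid and favourable change are chosen for illustration.

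Let a and b be the probability of favourable change without and with a keloid. The arm rates are then 0.45a + 0.55b (control) and 0.70a + 0.30b (injection).

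Full mediation, a = 0.90, b = 0.10:
- control 0.405 + 0.055 = 0.46; injection 0.63 + 0.03 = 0.66
- unadjusted OR = (0.66/0.34)/(0.46/0.54) = 2.28
- within each keloid stratum the arms have equal rates, so the adjusted OR = 1.00

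Partial mediation, control a = 0.80, b = 0.20, with a direct OR of 1.5:
- injection a: odds 4·1.5 = 6, so 0.857; injection b: odds 0.25·1.5 = 0.375, so 0.273
- control 0.36 + 0.11 = 0.47; injection 0.70·0.857 + 0.30·0.273 = 0.682
- unadjusted OR = (0.682/0.318)/(0.47/0.53) = 2.42; adjusted OR = 1.50

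**4. Summary.** Odds ratios are large-sample values. Power is from 2,000 simulated trials per row, 75 per arm.

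| Assumed link (a / b) | OR unadjusted | OR adjusted | Power unadjusted | Power adjusted |
|---|---|---|---|---|
| 0.80 / 0.20, no direct effect | 1.84 | 1.00 | 44% | 4% |
| 0.90 / 0.30, no direct effect | 1.94 | 1.00 | 48% | 4% |
| 0.90 / 0.10, no direct effect | 2.28 | 1.00 | 69% | 3% |
| 0.95 / 0.10, no direct effect | 2.44 | 1.00 | 77% | 3% |
| 0.80 / 0.20, direct OR 1.5 | 2.42 | 1.50 | 75% | 17% |
| 0.80 / 0.20, direct OR 2 | 2.93 | 2.00 | 90% | 37% |
| Change unrelated to keloid (45% v 70%) | 2.85 | 2.85 | 87% | 85% |

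Simulated median odds ratios for the second and fourth rows were 1.95 and 2.47 unadjusted, and 0.98 and 1.01 adjusted. The simulations contain no shared unmeasured cause, so they show only the loss of the mediated part and not the second problem.

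**The case against.** **It removes the whole effect.** A reader might infer that an effective injection would be reported as having no effect on the scar. The documents do not support that. An adjusted odds ratio of 1.00 follows by construction when scar change depends on keloid status alone. The protocol gives no figure for how much of the effect runs that way; with a direct effect some of it survives, and with no link none is lost.

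**The covariate nearly determines the outcome.** This too is tempting, since every woman enters with a keloid scar. But no figure links the two variables, and "changed" has no stated direction, so a larger regrown keloid could count as changed. At 90% v 30% the covariate is far from determining the outcome. Near separation is not established.

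**Other analyses cover the question.** This stands in part. The χ² comparison of keloid formation is unadjusted, so a benefit through preventing keloids would show there. The general sentence on binary outcomes may also give an unadjusted test of scar change. But the sentence written for this outcome prescribes the regression, and no rule says which result governs if the two disagree.

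**Scar change is not really primary.** The Interim analysis section calls keloid formation the primary outcome, and the Secondary objectives repeat scar appearance. The Composite primary outcome section still lists scar change as primary, so the point affects one of two primary outcomes.

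**A baseline count was meant.** The wording does not support this: it speaks of keloids formed, and the article uses keloid formation for the result after the intervention. If it was the intention, the sentence still needs correcting.

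**The SAP may settle it.** The precise list of demographic covariates can be left to an SAP and is not criticised here. The keloid covariate is different, because the article states it explicitly.

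**Conclusion.** The concern holds: the covariate is wrong as written. Adjusting scar change for keloids formed means the treatment coefficient is not the total intention-to-treat effect of allocation. It excludes the part acting through keloid formation and is open to bias from shared unmeasured causes. That conclusion rests on the text alone.

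The size is uncertain. Under the assumptions listed in the working, the loss ranges from none (scar change unrelated to keloid formation), through partial (2.42 to 1.50; 2.93 to 2.00), to complete under full mediation (about 1.8–2.5 to 1.0). None of these is a forecast for this trial. The analysis of keloid formation and the sample size are unaffected.

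**What to change.** In the Data analysis section, delete the keloid count from the covariates of the scar-change model. Adjust only for pre-specified variables measured before randomisation, for example the baseline scar measures already collected and demographics. State whether this model or the general χ² comparison governs for scar change. Any model that does adjust for keloids formed should be labelled exploratory. If a keloid count before surgery was intended, name it as a baseline variable.

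The cost is a sentence or two of text. No data collection or sample size changes.
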